#### Secondary outcomes

Parent–staff interactions: Assessed by the PEC survey.Staff workload: Staff members will be asked to complete a three-question Staff Survey:

In the last 24 hours, have you updated parents during a ward round? Y/NIn the last 24 hours, how many times have you spoken to parents face-to-face about their baby (outside ward round times)?In the last 24 hours, how many times have you spoken to parents over the phone?

EPR data completeness and accuracy (expressed in %): The lead researcher will compare EPR-recorded data to handwritten clinical documentation to produce a daily measure of data completeness.Qualitative evaluations: The lead researcher will conduct one-on-one in-depth interviews with parents (30 min) and staff members (10 min). Interviews will explore the parent experience of receiving information updates in neonatal care and feeling involved in their baby’s care (see online supplementary file 1). For staff, interviews will explore their experience of giving parents information updates and perceptions of how updating parents affects their workload (see online supplementary file 2). Interviews will be recorded and anonymously transcribed.

10.1136/bmjpo-2019-000515.supp1Supplementary data

10.1136/bmjpo-2019-000515.supp2Supplementary data

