## Abstract

**Introduction:**

Having a baby that requires neonatal care is stressful and traumatic. Parents often report dissatisfaction with communication of clinical information. In the UK neonatal care data are recorded daily using electronic patient record systems (EPR), from which deidentified data form the National Neonatal Research Database (NNRD). We aim to evaluate the impact of sharing neonatal EPR data with parents, on parent-reported satisfaction, parent–staff interactions, staff workload and data completeness.

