**Analysis:**

Primary outcome: parent satisfaction ‘with communication of clinical information and involvement in care’. Secondary outcomes: parent–staff interactions, staff workload, data completeness. Baseline survey data will be obtained from clinical service evaluation preceding the intervention. Baseline data completeness will be derived from the NNRD. During the intervention, surveys will be administered biweekly and data completeness assessed daily. We will analyse outcomes using run charts and partially paired statistical tests. Parent and staff interviews will explore information exchange and the communication tool’s impact.

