### Implementation of the intervention

#### Stage 1: ‘Proof of concept’ (2 weeks—SCBU, lowest intensity area)

We will recruit three parents from SCBU and administer an individualised *‘My Baby’s Summary Report’* to them in a sealed envelope every weekday, over 2 weeks. We will administer PEC and staff surveys at baseline, weekly and at the end, and we will assess EPR data completeness and accuracy daily.

Data analysis will be aimed at improving the *‘My Baby’s Summary Report’* template and the piloting process. We will use PDSA cycles^18–20^ to analyse parental free-text feedback from PEC surveys and adapt the report’s template, creating the final template version for use in Stage 2 ‘Roll-out’. We will plot the parent and staff survey data on run charts, a standard method of quality control and a useful tool in quality improvement that enables one to monitor the performance of a process over time.^21^

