#### Quantitative outcomes

For parent and staff outcomes, we will

Demonstrate how the outcomes change over time: For continuous variables derived from the PEC’s Likert scale questions we will use run charts (21). For categorical variables we will conduct a comparison of response distributions precommunication and postcommunication tool implementation.Evaluate the communication tool’s specific impact on outcomes: Using partially paired parent data, we will compare the difference in the outcomes of parent satisfaction, parent–staff interactions and staff workload from baseline to repeat measures, between the baseline measurement period (previous service evaluation assessment) and the trial intervention period. NNRD data completeness will be expressed in percentages, compared with 3-month historical NNRD baseline measures and analysed using run charts (21).

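### The data completeness outcome is defined against handwritten notes but its baseline comes from the NNRD, so the before-after comparison is either between unlike measures or not of the defined outcome

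*Protocol article*

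**What the plan says.** Secondary outcomes names completeness and accuracy of the EPR together, as a percentage, and describes one procedure: "The lead researcher will compare EPR-recorded data to handwritten clinical documentation to produce a daily measure of data completeness". Stage 1 repeats the combined label for the proof-of-concept weeks: "we will assess EPR data completeness and accuracy daily".

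The Abstract (Analysis paragraph) treats the two periods separately. For the period before the tool: "Baseline data completeness will be derived from the NNRD". For the period with the tool: "During the intervention, surveys will be administered biweekly and data completeness assessed daily".

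Quantitative outcomes states the comparison: "NNRD data completeness will be expressed in percentages, compared with 3-month historical NNRD baseline measures and analysed using run charts". Accuracy is not mentioned there.

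The Introduction describes the NNRD as a defined set of items extracted from the EPR, calls its completeness high without giving a figure, words the aim in terms of NNRD completeness, and includes higher data completeness in the hypothesis.

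**The concern.** Completeness of a database extract and completeness judged against handwritten notes are different quantities. The first asks whether expected fields are filled. The second asks whether the EPR agrees with another record of the same care, and that other record has gaps of its own. An item missing from both may count as missing in the first and go unseen in the second.

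A run chart shows a change of measuring method in the same way as it shows a change in practice. If the method changes when the tool is introduced, the two cannot be separated. At stake is one of the two parts of the hypothesis, and a result that the Discussion says will inform a later cluster randomised trial.

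**Working it through.** The article gives no percentage, target or sample-size calculation for this outcome, so there is no figure to reproduce. The check sets the statements side by side and then adds an illustration with assumed values.

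**Side by side**

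| Place | Quantity named | Source or reference | Period |
|---|---|---|---|
| Introduction (aim) | NNRD completeness | NNRD | not split |
| Abstract, Analysis | data completeness | NNRD | baseline |
| Abstract, Analysis | data completeness, daily | not named | intervention |
| Secondary outcomes | EPR completeness and accuracy, daily | handwritten notes | not named |
| Stage 1 | EPR completeness and accuracy, daily | not named | proof of concept |
| Quantitative outcomes | NNRD completeness | NNRD history | against baseline |

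The only daily measure with a described method is the notes comparison. No section describes a notes comparison at baseline, and none says how NNRD completeness is obtained during the intervention. Historical NNRD data are a deidentified extract, so they cannot by themselves give a notes-referenced baseline.

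*Reading 1: Abstract with Secondary outcomes.* The baseline is NNRD-derived and the intervention value is notes-referenced. The measures differ by period.

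*Reading 2: Quantitative outcomes with the Introduction's aim.* NNRD is compared with NNRD. The measures match, but the outcome defined under Secondary outcomes has no baseline and is not the quantity analysed.

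**How large could the shift be under Reading 1?** All inputs here are assumptions, and recording practice is held unchanged.

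*Illustration A.* Of 100 expected items, 10 are missing from the EPR, so field completeness is 90/100 = 90%. The notes hold 80 items. Let b of the 10 missing items also be absent from the notes. Then notes-based completeness = (80 - (10 - b))/80.

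- b = 0: 70/80 = 87.5%, a shift of -2.5 points
- b = 2: 72/80 = 90.0%, a shift of 0
- b = 5: 75/80 = 93.75%, a shift of +3.75
- b = 8: 78/80 = 97.5%, a shift of +7.5
- b = 10: 80/80 = 100%, a shift of +10

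If only 2 items are missing (field completeness 98%), the formula is (80 - (2 - b))/80. It gives 97.5% at b = 0 and 100% at b = 2, so the shift is -0.5 to +2 points.

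*Illustration B.* Let A be field completeness (85%, 90% or 95%). Let the chance that an item in the notes is also in the EPR be A - 5, A or A + 4 points. Let agreement between the two be 100% or 95%, the lower value applying if disagreement counts against the measure. Notes-based value = that chance × agreement.

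- Lowest: A = 95%, 0.90 × 0.95 = 0.855, a shift of -9.5 points
- Highest: (A + 4 points) × 1.00, a shift of +4.0 points at each A
- Chance equal to A with full agreement: a shift of 0

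With one measure in both periods and unchanged recording, the expected difference is 0 by construction.

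**The case against.** The strongest reply is that the only comparison the article spells out is NNRD against NNRD, which matches the aim in the Introduction. On that view the daily notes check is a separate monitoring measure, also used in the proof-of-concept stage, and no before-after claim is made for accuracy. This is a fair reading and it removes the artefact. It does not remove the inconsistency, because the defined outcome and the analysed quantity are then different things.

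A reader might also infer more than the text supports:

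- That the two series will be plotted on one run chart. No section says so.
- That the denominators, same-day timing and babies checked are known to differ. The article specifies none of these. A daily measure may mean one value per day of care, and such detail commonly sits in the full protocol. The two study figures are not shown and may bear on it.
- That a step at the start of the intervention would certainly appear. It could appear. Both measures start from the same EPR entries, and both illustrations include a shift of zero.

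The assumed 10% missing rate has no source in the document. If completeness is very high, the artefact shrinks, as the 98% case shows.

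**Conclusion.** The point holds as an inconsistency that must be reconciled. Under one reading the before-after difference mixes two measures, and a shift of unknown size and direction could arise with no change in recording. Under the other, the outcome defined under Secondary outcomes has no baseline and no stated comparison. Condensation for a journal does not explain this, because the article itself states both methods.

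Across the two illustrations the possible artefact runs from -9.5 to +10 points, and from -0.5 to +2 points when only 2% of fields are missing. These figures rest wholly on assumed values. They show that a shift is possible, not that it will be material.

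Severity is moderate. The outcome is secondary, the study is a small pilot, the analysis is by run chart, and the primary outcome is untouched. It still deserves correction because completeness is part of the stated hypothesis. To call it a fatal flaw would go beyond the documents, since a like-for-like NNRD comparison may be what the authors intend.

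**What to change.** Reconcile the Abstract, Secondary outcomes and Quantitative outcomes on one definition. For example:

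*Data completeness is the percentage of a fixed list of NNRD/EPR data items that are populated. It is taken from the NNRD/EPR extract in both the three-month baseline and the intervention weeks, using the same items, denominator, babies and lag between the day of care and extraction. It is shown on run charts. Agreement of EPR entries with handwritten notes is reported separately as a descriptive accuracy measure for the intervention period, with no before-after comparison.*

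The cost is a rewording of the outcome and its analysis sentence, one further extract covering the intervention weeks from a source the study already uses, and slightly more analysis. The daily notes check can continue as planned.

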### Implementation of the intervention

#### Stage 1: ‘Proof of concept’ (2 weeks—SCBU, lowest intensity area)

We will recruit three parents from SCBU and administer an individualised *‘My Baby’s Summary Report’* to them in a sealed envelope every weekday, over 2 weeks. We will administer PEC and staff surveys at baseline, weekly and at the end, and we will assess EPR data completeness and accuracy daily.

Data analysis will be aimed at improving the *‘My Baby’s Summary Report’* template and the piloting process. We will use PDSA cycles^18–20^ to analyse parental free-text feedback from PEC surveys and adapt the report’s template, creating the final template version for use in Stage 2 ‘Roll-out’. We will plot the parent and staff survey data on run charts, a standard method of quality control and a useful tool in quality improvement that enables one to monitor the performance of a process over time.^21^

#### Stage 2: ‘Roll out’ (6 weeks—SCBU 2 weeks—HDU 2 weeks—ITU 2 weeks)

We will recruit a maximum of 90 parents, administer *‘My baby’s Summary Report’* every weekday and conduct a qualitative and quantitative evaluation over 6 weeks, while also using quality improvement methodology to further improve the communication tool (figure 2).

**Figure 2 F2:**
[figure not shown]
Roll-out stage. PEC, parents’ experiences of communication in neonatal care.

### Analysis

#### Baseline measurement

Baseline measures for parent satisfaction and staff workload will be obtained from on-going evaluations undertaken as part of clinical service evaluation on the neonatal unit; these evaluations use the PEC survey and staff survey. Data from PEC and staff surveys from a 6-week period before the start of the trial will be used to generate baseline median values for each PEC survey item and staff survey questions using run charts (21).

#### Quantitative outcomes

For parent and staff outcomes, we will

Demonstrate how the outcomes change over time: For continuous variables derived from the PEC’s Likert scale questions we will use run charts (21). For categorical variables we will conduct a comparison of response distributions precommunication and postcommunication tool implementation.Evaluate the communication tool’s specific impact on outcomes: Using partially paired parent data, we will compare the difference in the outcomes of parent satisfaction, parent–staff interactions and staff workload from baseline to repeat measures, between the baseline measurement period (previous service evaluation assessment) and the trial intervention period. NNRD data completeness will be expressed in percentages, compared with 3-month historical NNRD baseline measures and analysed using run charts (21).

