The aim of this study is to use existing, routinely recorded data, from existing neonatal electronic patient record systems (EPR) to implement, further co-develop and evaluate a neonatal communication tool with parents. In the UK a defined set of data items are extracted from neonatal EPR systems to form the National Neonatal Research Database (NNRD).^14^ This holds information on all babies admitted for NHS neonatal care and is used for audit, benchmarking and research, but is currently not routinely shared with parents. The completeness of data in the NNRD is high^14^ but has the potential to further improve. There is a lack of evidence for interventions to improve the completeness of routinely collected data in neonatal care and more widely.

We will evaluate the impact of sharing routinely recorded infant information with parents, on parent satisfaction with ‘communication of clinical information and involvement in care’ using a validated questionnaire, and on the completeness of NNRD data extracted from neonatal EPR systems. We hypothesise that sharing individualised, daily EPR data with parents will lead to higher reported parent satisfaction and data completeness.

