### Communication tool

We previously identified the information parents report as important when their baby is on a neonatal unit through qualitative work with ex-neonatal parents. This information was matched to the routinely recorded neonatal daily EPR data items and we developed parent-friendly explanations of these EPR data items with parents. We co-designed a communication tool template for parents called ‘*My Baby’s Summary Report*’; this comprised a printed sheet of paper including individualised, daily infant updates for parents derived from EPR data, in parent-centred language.

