### Design

A prospective before-and-after study employing mixed methods. The intervention (the communication tool) will be implemented in stages across the three intensity unit areas of the Chelsea and Westminster hospital neonatal intensive care unit (from low to high) over an 8-week period; a 2-week proof of concept phase will precede a 6-week roll-out phase (figure 1). An individualised *‘My Baby’s Summary Report’* will be administered to recruited parents in a sealed envelope every weekday. Quality improvement methodologies, including Plan-Do-Study-Act (PDSA) cycles^18–20^ and run-charts^21^ will be used to implement and further improve the communication tool. The content and the exact timing of the implementation in relation to the study will be fully described to avoid other concurrent parent-centred interventions influencing our study results.

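### Data completeness is compared only with a historical NNRD baseline; tying it to the report's items and areas, with concurrent comparison series, would make the result readable

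*Protocol article*

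**What the plan says.** Higher completeness is part of the study hypothesis. The Introduction expects that "sharing individualised, daily EPR data with parents will lead to higher reported parent satisfaction and data completeness". The abstract and the Secondary outcomes section both list completeness as a secondary outcome.

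The comparator is stated twice. The abstract's Analysis paragraph says "Baseline data completeness will be derived from the NNRD", and Quantitative outcomes says "NNRD data completeness will be expressed in percentages, compared with 3-month historical NNRD baseline measures and analysed using run charts". No concurrent comparator for completeness is named. Secondary outcomes adds a daily measure during the intervention: "The lead researcher will compare EPR-recorded data to handwritten clinical documentation to produce a daily measure of data completeness". Whether that is the same measurement as the NNRD figure is a separate question and is not argued here.

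The reach of the report is narrower than the reach of the database:

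- **Items.** Under Communication tool, the content starts from what parents reported as important: "This information was matched to the routinely recorded neonatal daily EPR data items". The share of NNRD items this represents is not given.
- **Babies and days.** Under Design, the report "will be administered to recruited parents in a sealed envelope every weekday".
- **Areas.** Design, Participants and the Stage 2 heading describe a staged entry into SCBU, then HDU, then intensive care, at 2-week steps within the roll-out.
- **Database.** Of the NNRD, the Introduction says "This holds information on all babies admitted for NHS neonatal care".

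On the starting level, the Introduction says "The completeness of data in the NNRD is high", adds that it could still improve, and gives no figure for this unit.

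**The concern.** The intervention acts most directly on the records of certain babies, in areas already opened, for items that parents will see in print. The stated comparison sets NNRD completeness after the start against NNRD completeness in the preceding 3 months. Two problems can follow.

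First, if the percentage runs over all records and items of the unit, exposed records are averaged with records that the report does not touch. Where completeness is already high, the room for a rise is small, and averaging shrinks it further. A flat run chart could then be read as no effect when the effect was only diluted.

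Second, a rise could have another cause in the same weeks. Design and Discussion promise to describe other interventions, but only parent-centred ones. An audit drive, a change to the EPR or a turnover of staff lies outside that promise, and these are the events most likely to move recording. A run chart shows an existing trend. It cannot attribute a shift to one of two things that happened together.

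The study is meant to inform a later cluster RCT, so a completeness signal that is hard to read in either direction loses part of its use.

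**Working it through.** **No stated figure to reproduce.** The article gives no baseline percentage, target effect or sample size for completeness. The durations agree with each other: 2 + 6 = 8 weeks overall, and 4 + 2 + 2 = 8 weeks of recruitment by area.

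**Inputs from the article.** Three areas; a 6-week roll-out with 2-week steps (Stage 2 heading); weekday reports (Design); at most 90 parents (Stage 2); 36 cots and 750 admissions a year (Participants).

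**Assumptions.** Areas of equal size. At first, no change in recording for unexposed records.

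**Formula.** Change seen in a pooled percentage = true change in exposed records × exposed share.

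**Open area-weeks.** The total is 3 areas × 6 weeks = 18.

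- Cumulative, each area staying open once started: (6 + 4 + 2)/18 = 12/18 = 67%. The statement under Participants that HDU parents are recruited additionally points this way.
- Sequential, one area at a time: (2 + 2 + 2)/18 = 6/18 = 33%. The Stage 2 heading can be read this way.

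**If weekend records do not respond.** 12/18 × 5/7 = 48%; 6/18 × 5/7 = 24%. This factor is the softest, because a weekday report may also improve weekend entries.

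**Babies.** 750 × 6/52 ≈ 87 admissions in 6 weeks. Adding 36 occupied cots at the start (assumed full) gives about 123 babies. Ninety parents cover at most 90/123 = 73% of them, or 45/123 = 37% if both parents of each baby enrol. Non-consent and the language exclusion also limit coverage. The share of items printed is unknown; if it were half (assumed), a percentage over all items would halve every share above.

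**Size, for illustration.** Assume a 95% baseline and a tool that halves the gap, a gain of 2.5 points in exposed records:

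| Exposed share | Pooled change |
|---|---|
| 67% | 2.5 × 0.667 = 1.7 points |
| 48% | 2.5 × 0.476 = 1.2 points |
| 33% | 2.5 × 0.333 = 0.8 points |
| 24% | 2.5 × 0.238 = 0.6 points |

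The largest rise the pooled figure could show, if every exposed record became complete, is (100% − baseline) × share:

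| Assumed baseline | Share 48% | Share 24% |
|---|---|---|
| 85% | 7.1 points | 3.6 points |
| 90% | 4.8 points | 2.4 points |
| 95% | 2.4 points | 1.2 points |

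**Relaxing the no-spillover assumption.** Let s be the fraction of the effect that reaches unexposed records, and f the exposed share. The pooled change becomes true change × [f + s(1 − f)], and an exposed-minus-unexposed contrast becomes true change × (1 − s). With s = 0.5 and the 2.5-point gain:

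- Pooled, f = 67%: 2.5 × (0.667 + 0.5 × 0.333) = 2.1 points.
- Pooled, f = 33%: 2.5 × (0.333 + 0.5 × 0.667) = 1.7 points.
- Contrast: 2.5 × 0.5 = 1.25 points.

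Spillover therefore repairs the dilution but weakens the concurrent contrast. Neither display is sufficient alone, which argues for showing both.

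**The case against.** Four objections carry weight.

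*The text does not say that one percentage is taken over the whole unit.* Correct. It speaks of percentages in the plural, on run charts, with a daily measure that is also taken in a first stage with three parents. A reader might infer a single pooled NNRD figure, but the article does not state one, and an unstated denominator alone is a detail that a condensed article may leave to the full plan. The dilution is therefore conditional. What the article does fix is the comparator, which is historical only.

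*The absence of a control is the declared design.* Also correct. The title and Design say before-and-after, and the Discussion explains why randomisation was not used and points to a cluster RCT. A reader might infer that the completeness hypothesis cannot be answered at all. That goes too far: the 3-month baseline and run charts carry some information, and the result is weakly interpretable, not empty. However, the limitations discussed concern language, recruitment, parent factors and survey response. None concerns completeness.

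*Staff make the record, and may record better for every baby and item.* Nothing in the article rules this out, so it cannot be said that unexposed records are unable to respond.

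*Unexposed babies are a poor control.* Within open areas they are babies whose parents declined, were ineligible or were not reached. They share the unit and perhaps the staff. A reader might want exposed against unexposed babies as the main analysis; selection and spillover do not support that. Areas not yet opened also differ in intensity, so each should be read against its own baseline.

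**Conclusion.** The point holds in limited form. A historical comparison alone does not separate the tool from concurrent changes in recording practice, and the promised description of parent-centred co-interventions does not fill that gap. If completeness is pooled over all unit records and items without spillover, only 67% (cumulative) or 33% (sequential) of roll-out area-weeks are open, falling to 48% or 24% if weekends do not respond. Incomplete recruitment and unprinted items would reduce these shares further.

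These shares rest on equal area sizes. The changes in points rest on assumed baselines and effects, because the article gives neither. Full spillover would remove the dilution. This is a secondary outcome in a pilot, so the consequence is a rise or a null that is hard to interpret, not an invalid study. The change is still worth making because series that would help are largely in data the study already uses.

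**What to change.** In Quantitative outcomes, change the completeness analysis as follows:

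1. Define completeness on the items printed on the report. Compute it in the same way in the 3-month baseline and the intervention period, over the same areas and days of the week. If the template changes during the improvement cycles, state which item list applies.
2. Plot it by area, with each area's start date marked on its run chart.
3. On the same charts, add NNRD items not on the report, and areas not yet opened, as concurrent comparison series. A shift confined to printed items and following each area's start date would point to the tool; a shift in all series together would point to a common cause or to spillover.
4. Treat any contrast of recruited with non-recruited babies as supportive only, because of selection and spillover.
5. State that spillover may bias the concurrent contrasts toward no effect.

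The cost is analysis wording and some extra coding and plotting, with no added participants or procedures. If the NNRD extract does not identify the care area, a local EPR export is needed. The item and area series do not require flagging which parents consented. The optional contrast in step 4 does, and because the NNRD is deidentified it would need a local export and a check that existing approvals allow it.
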